### Participants

A total of 196 participants with IGT who are overweight/obese will be recruited from three different hospitals, Guang’anmen Hospital, Shenzhen Luohu District Traditional Chinese Medicine Hospital, and Yan Tai Hospital of Traditional Chinese Medicine, through public advertisements like posters, hospital websites, WeChat public accounts, and the Internet from October 2022 to December 2024. The research staff will introduce the background and process of the study in detail to potential subjects who contact the research team and express interest to participate. Once the informed consent form is signed, participants will be evaluated for eligibility by medical history inquiries, physical examinations, and necessary chemical examinations. The duration of the study for each participant will be 37 weeks, including 1-week baseline period, a 12-week treatment period, and a 24-week follow-up period.

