### Inclusion Criteria

Participants who meet all of the following criteria might be eligible: (1) those who meet the diagnostic criteria for overweight/obesity and IGT; (2) 18–60 years old; (3) those who can appropriately describe their wishes, voluntarily fill in the informed consent form, and agree to participate in clinical trials.

Note: The above three criteria should be met at the same time.

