### Randomization and Allocation Concealment

A random number will be generated with the SPSS software and concealed in opaque random envelopes. The envelopes will be prepared by a third party in advance, with the sequence number labeled on the surface and the random number and group allocation information sealed in. The random envelopes will be preserved by special personnel who are not involved in treatment and evaluation.

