### Outcome Measures

#### The Primary Outcome

The primary outcome will be change in the baseline value of 2hPG at the end of the 12-week treatment; 2hPG is the value of intravenous plasma glucose measured by 75 g OGTT, which is usually conducted to diagnose IGT and observe glucose metabolism (40). When the value of 2hPG fluctuates between 7.8 and 11.1 mmol/L, it will be regarded as IGT, and between 4.4 and 7.7 is the ideal control (40).

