### Sample Size Calculation

In this study, change in 2hPG from baseline will be used as the basis for primary sample size estimation, based on the unpublished preliminary data collected from 10 participants in the acupuncture group and 10 SA group controls (-1.16 ± 0.42 mmol/L VS0.97 ± 0.34 mmol/L), and a sample size of 196 participants (98 per group) will need to provide the trial with 80% power with a two-sided significance level of 0.05 and 10% dropouts. The PASS 15 software was used for sample size calculation.

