### Statistical Analysis

We will use the SPSS V.25 software (IBM Corp., Armonk, NY, United States) to perform all statistical analyses following the intention-to-treat principle. CI will be established at 95% and significance level at 0.05. Missing data will be calculated using the actual observational value without imputation if the dropout rate is no more than 5%. For continuous data, the data will be presented as mean ± *SD* if normally distributed or as median (IQR) if not normally distributed. Longitudinal continuous data will be compared between the groups by repeated-measures analysis of variance (ANOVA) including group and time–group interaction. Other continuous data will be analyzed by Student’s *t*-test and Wilcoxon rank-sum test, and categorical data by X ^2^ test or Fisher’s exact test, as appropriate. Linear correlation analysis will be conducted to measure the closeness of linear correlation between variables. Sensitivity analysis will be performed if necessary. A *p*-value < 0.05 will be considered statistically significant.

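### The stated analysis uses baseline 2hPG only by subtraction and lists no hospital term; adding both as covariates would gain precision at no cost

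*Protocol article*

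**What the plan says.** The Primary Outcome section defines the endpoint as a difference from baseline: "The primary outcome will be change in the baseline value of 2hPG at the end of the 12-week treatment". The Statistical Analysis section then names the method and its terms. Longitudinal continuous data go to "repeated-measures analysis of variance (ANOVA) including group and time–group interaction". For the rest, "Other continuous data will be analyzed by Student’s" t-test or the rank-sum test. Neither there nor elsewhere does the article list a baseline covariate or a hospital factor.

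Both variables are available for everyone. Baseline 2hPG is part of eligibility: the Inclusion Criteria admit "those who meet the diagnostic criteria for overweight/obesity and IGT", and the Diagnosis Criteria set the 2hPG window at 7.8 to 11.1 mmol/L. Participants "will be recruited from three different hospitals", so hospital is recorded by design.

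**The concern.** A change score fixes the slope of week-12 2hPG on baseline 2hPG at exactly 1. When the true slope is below 1, as is likely when people are selected for a raised value and some regress towards the mean, the change score still carries baseline variation that a covariate would remove. The treatment comparison then has a larger standard error than the same data could give, and a chance baseline difference between the groups is only partly corrected. At stake is the width of the confidence interval for the primary comparison, and some protection if the planning SD proves too small. Leaving out hospital could have a similar but lesser effect if mean change differs between hospitals.

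**Working it through.** **Inputs from the article (Sample Size Calculation).** There are 98 per group with 10% dropout, so 98 × 0.9 ≈ 88 evaluable per group. The SDs of change are 0.42 and 0.34, from 10 participants per group. After a leading minus sign, the pilot means and SDs are printed as "1.16 ± 0.42 mmol/L VS0.97 ± 0.34 mmol/L".

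**Assumptions not in the article.** The correlation rho between baseline and week-12 2hPG is shown over a range. Variances at the two times are taken as equal. The target difference is taken as 1.16 − 0.97 = 0.19 mmol/L, which supposes that a minus sign before 0.97 was lost. As printed, the difference is 2.13.

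**The plan's own figure.** Pooled SD = √((0.42² + 0.34²)/2) = √0.146 = 0.382. For 80% power at two-sided 0.05, n = 2 × (1.960 + 0.842)² × 0.146 / 0.19² ≈ 63.5, so 64 per group (65 by the t-test). After dropout that is 72–73 per group, or 144–146 in total, not 196. A difference of 2.13 needs only 2–4 per group after dropout. So 196 is not reproduced, which is a separate point. Of the two readings, only 0.19 comes near it, so it is used here for illustration.

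**Why adjustment does not lose precision.** Let beta be the slope of week-12 on baseline 2hPG. The variance of the change score minus the ANCOVA residual variance is (1 − beta)² × Var(baseline), which is never negative. The only cost is a trivial loss of degrees of freedom. With equal variances beta = rho, and the ratio is (1 − rho²)/(2(1 − rho)) = (1 + rho)/2.

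**Unadjusted reference.** SE = 0.382 × √(2/88) = 0.0576. Then 0.19/0.0576 = 3.30, and power ≈ Φ(3.30 − 1.96) = 91%.

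**Sensitivity to the pilot SD.** With 18 degrees of freedom, the upper 95% limit of the SD is 0.565. Unadjusted SE = 0.565 × √(2/88) = 0.0852, and power ≈ Φ(2.23 − 1.96) = 61%.

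**With baseline as covariate** (SE multiplied by √((1 + rho)/2)):

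| rho | variance ratio | SE at SD 0.382 | power at SD 0.382 | power at SD 0.565 |
|---|---|---|---|---|
| none (change score) | 1 | 0.0576 | 91% | 61% |
| 0.3 | 0.65 | 0.0464 | 98% | 79% |
| 0.5 | 0.75 | 0.0499 | 97% | 73% |
| 0.7 | 0.85 | 0.0531 | 95% | 68% |
| 0.9 | 0.95 | 0.0561 | 92% | 63% |

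At rho 0.5 the gain equals an unadjusted trial with 88/0.75 ≈ 117 per group.

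**Which rho is plausible?** With equal variances, rho = 1 − 0.146/(2 × baseline variance). If baseline 2hPG were spread evenly over the 3.3 mmol/L entry window, its SD would be 3.3/√12 = 0.95, rho about 0.92 and the gain about 4%. If the baseline SD were 0.5, rho would be about 0.71 and the gain about 15%.

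**Effect of a chance baseline imbalance.** An imbalance d shifts the change-score estimate by (1 − rho)d in size. A one-standard-error imbalance therefore shifts it by 0.0576 × √((1 − rho)/2) = 0.034, 0.029, 0.022 and 0.013 mmol/L at rho 0.3, 0.5, 0.7 and 0.9.

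**Hospital alone.** If hospital explained an assumed 2%, 5% or 10% of the variance of change, power at SD 0.382 would be 91.5%, 92.3% or 93.5%.

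**The case against.** The strongest reply is that this is only a preference for efficiency. A change-score comparison in a randomised trial is unbiased, and at 0.19 mmol/L with the pilot SDs it already has about 91% power against the 80% planned. The gain could be as little as 4–5% of variance. All of that stands.

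It can also be said that the list of terms is introduced as inclusive and does not even name the time main effect, so covariates may be left to an analysis plan that is not shown. That is possible. But the article goes beyond silence: it names a method, its terms and the fallback tests, and baseline adjustment would change what is written.

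Some stronger readings are tempting, and the documents do not support them:

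- **Baseline is ignored.** It is not; it enters by subtraction.
- **A small baseline imbalance could create or hide the effect.** On the figures above, a shift of 0.19 would need an imbalance of about 5.6 standard errors at rho 0.3 (0.19/0.034), and more at higher rho.
- **The trial is looking for 0.19 mmol/L.** The article never states this figure. It is an assumption, and the variance ratios do not depend on it.
- **Allocation is unstratified, and the hospitals differ in laboratories.** The article says only "A random number will be generated with the SPSS software and concealed in opaque random envelopes". A condensed description does not establish simple randomisation, and nothing is said about laboratories. No imbalance probability by hospital can be drawn from this, and no change to the randomisation is asked for.

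**Conclusion.** The point holds as a missed gain in precision. The stated analysis has neither a baseline covariate nor a hospital factor, and baseline adjustment is at least as precise as the change score apart from a trivial loss of degrees of freedom. Its size is uncertain, because the reduction of 5–35% in variance rests on equal variances and an unknown rho. With the pilot SD of 0.382, the lower part of that range is more likely if baseline values are widely spread over the entry window. The practical value is greatest if the pilot SD is too low: at the upper limit of 0.565, power goes from 61% to 63–79%. A reader might infer that the primary result would be biased or that the design is underpowered because of this omission, and neither follows. The hospital term is a minor addition with an unknown, probably small, gain.

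**What to change.** Add one sentence to the Statistical Analysis section: week-12 2hPG, and each other continuous outcome with a baseline measurement, will be compared between groups by ANCOVA, or by a mixed model for repeated measures, with the outcome's own baseline value as covariate and hospital as a three-level factor. For 2hPG, name the week-12 contrast as the primary estimate. With baseline in the model, week-12 value and change from baseline give the same treatment difference, so the primary outcome's definition need not change. Settle this before unblinding, so that there is no later choice between adjusted and unadjusted results. It needs no new data, visits or participants.

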### Diagnosis Criteria

The trial will adopt the diagnostic criteria of the World Health Organization [WHO (39)] for IGT (40) and the diagnostic criteria for overweight/obesity in the guidelines for the Prevention and Control of overweight and Obesity in Chinese Adults formulated by the Ministry of Health of China in 2003 (41, 42):

(1)IGT: fasting blood glucose (PG) is lower than 7 mmol/L, and 2-h blood glucose (2hPG) after oral 75 g glucose tolerance test (OGTT) is between 7.8 and ∼11.1 mmol/L.(2)overweight: 24 < BMI ≤ 27.9, obesity: BMI ≥ 28, or BMI ≤ 24 but waist circumference ≥ 85 cm (men)/ ≥ 80 cm (women).

Note: The above two criteria should be met at the same time.

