#### Secondary Outcomes

(1) Change from baseline value of 2-h blood glucose on weeks 24 and 36.

(2) Proportion of participants whose 2-h blood glucose dropped to normal from baseline on weeks 12, 24, and 36.

(3) Proportion of participants with at least 5% reductions (47) in body weight from baseline on weeks 4, 8, 12, 16, 24, and 36.

(4) Change from baseline of body mass index (BMI) and waist-to-hip ratio (WHR) on weeks 4, 8, 12, 16, 24, and 36.

(5) Change from baseline of fasting plasma glucose (FPG), fasting serum insulin (FINS), homeostasis model assessment-insulin resistance index (HOMA-IR), TC (serum total cholesterol), TG (triglyceride), LDL-C (low-density lipoprotein cholesterol), and high-density lipoprotein cholesterol (HDL-C) on weeks 12, 24, and 36.

(6) Change from baseline of blood pressure on weeks 12, 24, and 36.

(7) Change from baseline in the Impact of Weight on Quality of Life-Lite Questionnaire (IWQOL-Lite) scores on weeks 4, 8, 12, 16, 24, and 36.

IWQOL-Lite is an international scale used to measure an individual’s health-related quality of life (48). A total of 31 questions are divided into five subscales: 11 questions concerning physical function, 7 concerning self-esteem, 4 concerning sex life, 5 concerning public pressure, and 4 concerning work. The score of each question is divided into five grades, with 5 representing always, 4 often, 3 sometimes, 2 rarely, and 1 never. The total score of the questionnaire is 155, with higher score indicating worse quality of life. The MCID of IWQOL-Lite is 12 (49) for overweight/obesity.

(8) Change from baseline in the Simplified Nutritional Appetite Questionnaire (SNAQ) scores on weeks 4, 8, 12, 16, 24, and 36.

The SNAQ scale is a short and simple appetite assessment tool that can predict weight loss in adults (50). It measures the amount of food per meal, the number of meals per day, and the taste of the food. It consists of four items, each with five grades and with the total score ranging from 4 to 20 points. Lower scores indicate deterioration in appetite (50).

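### Normalisation of 2-h glucose is tested by an unadjusted X² or Fisher test although its threshold is also the entry limit; adjusting for baseline 2hPG would gain precision, by an amount the protocol does not determine

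*Protocol article*

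**What the plan says.** The Statistical Analysis section of the protocol article gives one rule for binary outcomes, as for all categorical data: an X² test or "Fisher’s exact test, as appropriate". It names no covariate, stratification or model for them; the only other provision is sensitivity analysis if needed.

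Secondary outcome (2) is "Proportion of participants whose 2-h blood glucose dropped to normal from baseline on weeks 12, 24, and 36". For entry, the Diagnosis Criteria require that 2hPG after the OGTT "is between 7.8 and ∼11.1 mmol/L". The Primary Outcome section gives the same range for IGT and adds that "between 4.4 and 7.7 is the ideal control". Normal is therefore read here as below 7.8 mmol/L, the point at which eligibility begins.

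**The concern.** A participant who enters at 7.9 mmol/L counts as normalised after a fall of just over 0.1; one who enters at 11.0 needs more than 3.2. If falls are typically about 1 mmol/L, as in the pilot, the starting value strongly affects who can normalise. The planned test compares two raw proportions and leaves this known source of variation in the error.

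At stake is the precision of the one listed outcome that directly measures the aim, given in the Discussion, of returning glucose to normal. Baseline 2hPG is already measured in everyone, because eligibility and the primary outcome both need it.

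**Working it through.** **Inputs from the Sample Size Calculation section**
- Pilot changes, 10 per arm: "1.16 ± 0.42 mmol/L VS0.97 ± 0.34 mmol/L", with a minus sign printed before the first mean. The second mean is read as -0.97 (assumed lost sign) and the ± values as SDs. The implied effect is 1.16 - 0.97 = 0.19 mmol/L.
- "a sample size of 196 participants (98 per group") and "80% power with a two-sided significance level of 0.05 and 10% dropouts". Evaluable per arm: 98 × 0.9 ≈ 88.

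**Assumed, because the article does not give them:** the baseline distribution within 7.8-11.1, the slope of follow-up on baseline, and normally distributed changes.

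**The plan's own figure.** The article states no power or rate for outcome (2). Its only figure, 196, concerns the primary outcome and is not reproduced by these inputs. With pooled SD √[(0.42² + 0.34²)/2] = 0.382, n = 2(1.96 + 0.842)² × 0.382²/0.19² ≈ 64 per arm. That becomes 72 after dropout, or 144 in total. This is a separate matter; 88 per arm is used below because it is the size the trial plans to have.

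**Direct calculation for one case: uniform baseline, slope 1, pilot SDs**
1. Proportions normalised: 1.16/3.3 = 0.352 and 0.97/3.3 = 0.294. The difference is 0.19/3.3 = 0.058.
2. Unadjusted SE: √[(0.352 × 0.648 + 0.294 × 0.706)/88] ≈ 0.070.
3. Adjusted variance: {E[p₁(1-p₁)] + E[p₀(1-p₀)]}/88 + Var(p₁-p₀)/176, where p₁ and p₀ are the chances of normalising given baseline. For a uniform baseline, E[p(1-p)] ≈ (1/√π) × SD/3.3, which is 0.0718 for SD 0.42 and 0.0581 for SD 0.34. The first term is 0.1299/88 = 0.00148 and the last about 0.00003. The SE is about 0.039.
4. Variance ratio, adjusted to unadjusted: 0.0388²/0.0703² ≈ 0.30. Simulation gave 0.31 (SE 0.0702 to 0.0393).
5. Power: 0.0576/0.0703 = 0.82 standard errors gives about 13%; 0.0576/0.0388 = 1.48 gives about 32%. Simulations gave 12-13% and 32-33%.

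**Varying the assumptions** (88 per arm; uniform, truncated-normal and right-skewed baselines):

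| Slope | SD, acupuncture / sham | Adjusted/unadjusted variance |
|---|---|---|
| 1 | 0.42 / 0.34 (pilot) | 0.31-0.44 |
| 1 | 0.77 / 0.62 (upper 95% limits of the pilot SDs) | 0.53-0.69 |
| 1 | 0.8-1.5 | 0.57-0.92 |
| 0.5 | 0.42 / 0.34 | 0.59-0.81 |
| 0.5 | 0.8-1.5 | 0.84-0.98 |

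At slope 0.5 the SD is the residual SD around the regression on baseline.

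In the first row, power for the 0.19 effect rises from about 12-23% to 32-46%. At slope 0.5 with SD 1.0 it moves only from about 15-16% to 16-17%.

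**Error rate.** With no effect, the adjusted test rejected in about 4-7% of simulated trials and X² in about 4-6%.

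**A check on the low slope.** With slope 0.5, the SD of change is at least 0.5 × SD of baseline. A uniform baseline has SD 0.95, so the floor is about 0.48, already above the pilot's 0.42. The pilot SDs thus sit more easily with a slope near 1, but they rest on 10 participants per arm.

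**The case against.** Four points weigh against this.

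- **The planned test is valid.** Allocation is randomised 1:1, so X² keeps its error rate. A reader might infer that a chance baseline imbalance could pass for an effect because of this test. The documents do not support that: such results are part of the ordinary 5% type I error, and adjustment does not lower that rate. This stands.
- **The size is uncertain.** A reader might infer that much of the precision is certainly lost. That needs a slope near 1 and SDs near the pilot's. Participants are selected on an OGTT value within a range, so regression to the mean is plausible, and the true SD may well exceed that of 10 per arm. This stands as a limit on size. It does not remove the point, since adjustment did not increase the variance in any scenario run.
- **The repair does not make the outcome well powered.** For an assumed 0.5 mmol/L effect at the pilot SDs, power would rise from about 54% to 97%, but that effect appears nowhere in the documents. At 0.19 the adjusted test still has only about 32-46% power in the most favourable row.
- **The outcome is one of many secondary ones, and covariates are often left to an analysis plan.** This limits the weight of the point. The article nevertheless names the test itself, so the point concerns a stated choice, not an omission.

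**Conclusion.** The point holds as an efficiency improvement. The plan fixes an unadjusted test for a responder outcome whose threshold is the entry limit of the same variable. Adjusting for baseline would leave between about 0.31 and 0.98 of the unadjusted variance. At the favourable end (1/0.44 to 1/0.31) this is worth roughly 2.3 to 3.2 times the sample size for this outcome; at the other end it is negligible.

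Where the trial falls depends on the baseline distribution, the slope and the SD of change, none of which the article settles. The figures also rest on the assumed minus sign, on normal meaning below 7.8, and on 88 evaluable per arm. They model week 12; at weeks 24 and 36 the link to baseline, and so the gain, could differ. The primary analysis of mean 2hPG change is not affected, and no bias is alleged.

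**What to change.** For outcome (2) at weeks 12, 24 and 36, prespecify a logistic regression at each visit on treatment group and continuous baseline 2hPG, and report the standardised (marginal) risk difference with its 95% CI. Keep the raw proportions as description, and X² or Fisher as a supporting analysis or as the fallback if the model cannot be fitted. Settle this before unblinding.

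The cost is about one sentence of analysis text, a standard SPSS procedure and a standardisation step, with no new data, visits or participants. The one small drawback is that the conditional odds ratio from the model differs from the crude odds ratio; reporting the standardised risk difference avoids that.

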## Discussion

The disease of diabetes is a global killer and ranks among the top causes of premature death, with 1 in 10 adults living with it and almost half undiagnosed, and obesity is an independent risk factor. People with diabetes are more vulnerable to the COVID-19 and might develop more comorbidities if they are infected (3, 16–18). There is an apparent need to detect diabetes early and preferably to initiate an action during the IGT stage to reverse blood glucose to normal level through appropriate intervention. The principle of preventing the disease before onset is highly valued in the theories of traditional Chinese medicine (57). Stimulating specific points (acupoints) by acupuncture can induce the special sensation of “*de qi*” (such as soreness, numbness, heaviness, and distension) to regulate the circulation of *qi* through meridians, thus regulating viscera function and metabolism of glucose and lipid. Previous animal experiments have shown that the acupoints CV4 and SP6 can activate SIRT1/PGC-1α in skeletal muscle (37) and regulate the expression of key insulin signaling-related molecules, thus relieving insulin resistance in obese diabetic mice (58). Stimulating the acupoints CV12 and ST40 may influence SIRT1 in the hypothalamic arcuate nucleus, inducing an anorectic effect and reducing obesity with IR (59). Additionally, ST25 could also regulate the activity of glucose-inhibited neurons in the lateral hypothalamic area and improve the secretory function of adipose tissue to regulate glucose and lipid metabolism (60). This is the first randomized, multicenter and parallel trial to evaluate the efficacy and safety of acupuncture in improving glucose metabolism among IGT participants who are overweight or obese. It may provide valuable clinical evidence for the treatment of IGT and the prevention of diabetes.

However, some limitations of our study should be acknowledged. First, because of the characteristics of acupuncture, the acupuncturist will not be blinded in our trial, which may cause a potential bias. Second, the use of sham acupoints and minimal acupuncture without any manipulation may cause some biological effects leading to false-negative results. The settings of SA need considerations on how to avoid physiological effects as much as possible while blinding the participants. Acupuncture is a penetrating operation, and acupuncture marks will be left on participants’ body after the needle is withdrawn. Since most of the acupoints in this scheme are in the abdomen and limbs, it is convenient for participants to see whether any acupuncture marks are left after acupuncture. Therefore, to ensure blindness of the participants, we use sham acupoint and micro-acupuncture as a placebo control. However, it is difficult to avoid the non-placebo effect of sham needles, as a slight stimulus or a stronger stimulus of gentle touch may lead to different degrees of neurological responses.

